**Methods:**

This single-blinded, single-center, randomized controlled trial will include 88 females who have not yet started the early or middle stage of the chemotherapy cycle. A random number table will be used randomly assign females to the intervention group or usual group at a 1:1 ratio. The intervention elements are based on the theoretical guidance of the Integrated Theory of Health Behavior Change (ITHBC). A multidisciplinary team (MDT) comprising oncologists, dietitians, nurses, traditional Chinese medicine (TCM) practitioners, and psychologists will provide the intervention. Intervention sessions will be conducted once a week for 8 weeks, beginning in the early or middle stage of the chemotherapy cycle and continuing through admission and a home-based interval chemotherapy period. The intervention includes face-to-face discussions, online meetings, WeChat messaging, and telephone calls. The themes target adverse reactions, dietary information and habits, self-care self-efficacy, treatment self-regulation, dietary supplement and TCM use, social support, weight management, and outcome expectations. The primary outcome is dietary management behavior measured by the Dietary Management Behavior Questionnaire (DMBQ). Secondary outcomes are self-care self-efficacy assessed by the Strategies Used by People to Promote Health (SUPPH); quality of life measured by the Functional Assessment of Cancer Therapy-Breast (FACT-B); and body mass index (BMI) measured by an electronic meter. All participants will be assessed at baseline and immediately, 1 month, 3 months, 6 months, and 12 months after the intervention.

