### Sample size

G power software will be used to calculate the sample size of the study, and ANOVA and a priori power analysis were selected [27]. Because there is little relevant literature and most multidisciplinary health management interventions do not report detailed sample size calculation parameters, we adopted system default parameters, including an effect size of 0.25, a power of 0.95, and an α of 0.05. After calculation, the total sample size was 72, with 36 participants in each group. Considering a 20% loss-to-follow-up rate, we obtained a final sample of 44 participants per group.

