### Outcome and measurements

We determined the intervention outcomes based on the theoretical guidance of the ITHBC, which states that patients’ knowledge and beliefs, self-regulation, and social support may influence their health behavior (proximal outcome) and health status (distal outcome). The primary outcome of this intervention is dietary management behavior. The secondary outcomes are psychological and physiological health status. The effect of the intervention will be compared with that of the control, both as a primary and secondary outcome. Each indicator is an independent metric.

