### Primary outcome

**Dietary management behavior.** The patient-reported Dietary Management Behavior Questionnaire (DMBQ) will be used to assess dietary management behavior in BC patients treated with chemotherapy. Our group members previously developed this questionnaire in 2023 based on the theoretical guidance of the ITHBC and the Capacity, Opportunity, Motivation-Behavior Model (COM-B) [33]. After conducting a scoping review to construct an item pool, three rounds of a multicenter survey were completed, including item selection and evaluation of the reliability, validation, and discriminative ability of the formal verified version. This tool comprises 4 domains and 22 items, including the adverse reaction coping (4 items), dietary information acquisition (5 items), dietary habit regulation (8 items), nutritional supplements, and dietary replacement (5 items) domains. The items are rated on a 5-point Likert scale ranging from ‘strongly disagree’ (1 point) to ‘strongly agree’ (5 points), with higher scores indicating better DMB. The structure was tested among 760 Chinese BC patients treated with chemotherapy from three hospitals. The total cumulative variance contribution rate of the 4 domains and the 22-item questionnaire was 62.67%, the Cronbach’s α coefficient was 0.908, the split-half reliability coefficient was 0.833, and the test-retest reliability coefficient was 0.938. Moreover, there were significant differences in the average scores of each dimension among patients with different ages, education levels, BMIs, menopausal statuses, and histological stages (all *P* < 0.05), and these differences were reflected in different pairwise comparison groups, indicating good reliability, validation and discriminative ability in BC populations.

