### Statistical analysis

We will use IBM SPSS Statistics 21.0 software to analyze the statistical data. Descriptive statistics, such as the number of patients with different ages, education levels, cancer stages and types of chemotherapy, as well as the percentage of patients in different groups relative to the total number of patients, will be calculated for different groups of demographic and clinical information. The mean and standard deviation will be used to compare the DMBQ total and dimensions scores, the SUPPH and FACT-B scores, and BMI. To compare the baseline balance between the two groups, two independent sample *t* tests, chi-square tests or Mann‒Whitney U tests, will be used, depending on whether the data distribution satisfies homogeneity of variance. The Shapiro‒Wilk test will be used to verify whether the scores of the two groups at different time points follow a normal distribution. If the data are balanced, repeated ANOVA will be adopted. Otherwise, we will use a generalized estimating equation (GEE) to analyze the intervention’s time, group, and interaction effects [36]. For all the above tests, *P* < 0.05 will indicate a statistically significant difference, the α level will be 0.05, and the tests will be two-sided. We will use intention-to-treat (ITT) analysis to minimize bias for sensitivity analysis [37]. The results of the last measurement of the patients who drop out of the study will be taken as the effect, which assumes that they complete the intervention, and the analysis will be reconducted with the GEE. Furthermore, missing data will be imputed with the mean values of the characteristics or with the help of multiple imputation methods if they are random and unrelated to the research elements.

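### The protocol judges the time, group and interaction effects each at an unadjusted 0.05 and does not say which decides the primary outcome; if group or interaction on the DMBQ total may decide, the false-positive risk is about 10%, not 5%

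*Protocol article*

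**What the plan says.** - **Primary outcome.** Outcome and measurements: "The primary outcome of this intervention is dietary management behavior". It is measured with the DMBQ, of which the Primary outcome section says: "This tool comprises 4 domains and 22 items".
- **Visits.** Abstract, Methods: "All participants will be assessed at baseline and immediately, 1 month, 3 months, 6 months, and 12 months after the intervention". That makes six visits, T0 to T5. None is named as primary.
- **Effects.** Statistical analysis plans a repeated-measures ANOVA or, failing that, a GEE. The effects named are "time, group, and interaction effects".
- **Threshold.** The same section applies P < 0.05 to all the tests it has listed; this "will indicate a statistically significant difference, the α level will be 0.05, and the tests will be two-sided". No order or adjustment is given.
- **Scores.** "The mean and standard deviation will be used to compare the DMBQ total and dimensions scores", together with SUPPH, FACT-B and BMI. This sentence names summary statistics, not a test.
- **Relation between outcomes.** "Each indicator is an independent metric". In context this concerns primary and secondary outcomes. It sets no order among tests within the DMBQ.
- **Sample size.** The inputs are "an effect size of 0.25, a power of 0.95, and an α of 0.05", for an ANOVA whose deciding effect is not identified.

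**The concern.** The three effects answer different questions.

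- **Time** asks whether scores change in the two arms together. The Discussion itself says that chemotherapy changes diet early and that the changes persist, so a time effect can appear with no benefit of the intervention.
- **Group** asks whether the arms differ on average over all visits in the model. In a pretest and follow-up design that may include T0, when no intervention effect can yet exist.
- **Interaction** asks whether the two profiles over time differ in shape.

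With each held to 0.05 and none named as deciding, the trial has at least two treatment-related routes to a positive primary result. The 5% error rate used for the sample size belongs to one test, so it is kept only if one test decides. The choice also affects power, because the group effect and the interaction are not equally sensitive to the same benefit.

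**Working it through.** **1. The plan's own figures.** One test at 0.05 keeps its level: in 10,000 simulated null trials per setting (72 patients, six visits), the interaction on the DMBQ total was significant in 4.5–5.3%.

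The planned total of 72 does not identify the test. Taking the effect size as Cohen's f = 0.25, with two groups, power 0.95 and α 0.05:

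| Test | Required total |
|---|---|
| One-way ANOVA, two groups | 210 |
| Between-group effect, 6 measurements, correlation 0.5 | 124 |
| Interaction, 6 measurements, correlation 0.5 | 28 |

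The number of measurements and the correlation used in the calculation are not stated. 72 is reached only with particular choices, for example the between-group effect with six measurements and correlation 0.2.

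**2. Error rate on the DMBQ total.** For k independent tests at 0.05, the chance of at least one false positive is 1 − 0.95^k. For group and interaction, k = 2: 1 − 0.95² = 0.0975. Simulation under no group difference and no time trend, with between-visit and between-dimension correlations each varied over 0.3, 0.5 and 0.7 (assumptions), gave 9.4–10.4%. A repeat at 88 patients and between-visit correlations 0.3, 0.5 and 0.7 gave 9.8%, 10.5% and 9.9% (20,000 trials each).

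**3. Conditional case: dimensions also tested and counted.** Two effects on five scores make ten tests. The independence ceiling is 1 − 0.95¹⁰ = 0.401. With correlated dimensions and the total as their item-weighted sum, simulation gave 25–33%.

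**4. What each candidate test can detect.** Assumptions: 44 per arm, no dropout, SD 1, a constant difference of 0.5 SD at T1–T5 and none at T0 (for two groups, f = 0.25 corresponds to 0.5 SD), equal correlation ρ = 0.5.

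- *Baseline-adjusted mean of T1–T5.* Variance of the mean: (1 + 4ρ)/5 = 0.60. Less the part explained by baseline, ρ² = 0.25: 0.35. Standard error √(0.35 × 2/44) = 0.126. Ratio 0.5/0.126 = 3.96. Power about 97%.
- *Group main effect with T0 in the model.* Difference 0.5 × 5/6 = 0.417. Variance (1 + 5ρ)/6 = 0.583. Standard error √(0.583 × 2/44) = 0.163. Ratio 2.56. Power about 72%.
- *Interaction.* Squared deviations of the six differences from their mean: 5 × 0.0833² + 0.417² = 0.208. Noncentrality 22 × 0.208/0.5 = 9.17 on 5 and 430 degrees of freedom. Power about 63%.
- *Baseline-adjusted difference at T1 alone.* Variance 1 − ρ² = 0.75. Standard error √(0.75 × 2/44) = 0.185. Ratio 2.71. Power about 76%.

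The same formulas at other correlations:

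| ρ | Adjusted T1–T5 mean | Group with T0 | Interaction | Adjusted T1 |
|---|---|---|---|---|
| 0.3 | 97% | 85% | 47% | 68% |
| 0.5 | 97% | 72% | 63% | 76% |
| 0.7 | 99% | 61% | 87% | 90% |

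Under a constant effect, the adjusted average is the most powerful of the four throughout.

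**The case against.** The protocol names one primary outcome and one instrument. A general two-sided 0.05 is a routine convention, and a primary time point or multiplicity rule is often left to an analysis plan, which is not shown here. The Discussion also calls the study preliminary and mainly about feasibility. Three stronger readings do not survive this objection:

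- **Six visits multiply the tests.** A reader might infer this, but the planned effects are omnibus over visits. The t tests in the section are for baseline balance, and no group test at each follow-up visit is specified.
- **The dimensions are further routes to success.** The section mentions them only for means and standard deviations. Testing them is a natural inference, since no other analysis is given for them, but it is not stated.
- **A significant time effect would count as success.** No passage says so, and Outcome and measurements frames the claim as a comparison with control. The wording that lists time among the intervention's effects is loose and is not a success rule.

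What remains is not mere silence. The section lists several effects and assigns each the same threshold, and the sample-size statement does not settle which one decides. The feasibility remark lowers the stakes, but the Background also states effectiveness on dietary behavior as an aim. It is also fair to say that a baseline-adjusted average is a different analysis from the planned model terms, so adopting it is more than a change of label.

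**Conclusion.** The point holds in limited form. The protocol does not fix which test decides the primary outcome, and it judges each listed effect at an unadjusted 0.05. On the DMBQ total, letting either group or interaction decide gives about 10% instead of 5%. This figure is stable over the correlations tried.

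The 25–33% figure applies only if the dimension scores are tested and counted as success. A general statement that the error rate is far above 5% is therefore not supported. If one effect on the total decides, the error rate is about 5% and the remaining fault is that the protocol does not say which.

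The power comparison rests on a constant 0.5 SD effect, equal correlations and complete data. An effect that fades after T1 would narrow or reverse the advantage of the average over a single early visit.

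**What to change.** Before outcome data are seen:

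1. Name one confirmatory test on the DMBQ total at two-sided 0.05. Preferred: the baseline-adjusted group difference averaged over T1–T5. If the intended claim is about the immediate effect, use the baseline-adjusted difference at T1 instead, but not both.
2. Report the interaction, visit-specific differences, the four dimension scores, SUPPH, FACT-B and BMI as secondary, with confidence intervals.
3. State that the time effect is descriptive.
4. Restate the sample size for the named test, giving the number of measurements and the correlation assumed.

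If the sponsor prefers to keep the planned terms, the minimum is to name either group or interaction on the total as deciding, or to test each at 0.025.

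The cost is small: no added patients, visits or data. Fewer results can be called confirmatory, the model statement changes if the adjusted average is adopted, and the power calculation must be redone for that test.

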
### Criteria for discontinuing or modifying allocated interventions

According to the criteria for discontinuing allocated interventions, the intervention will be discontinued when the participants ask to withdraw or when their health conditions worsen. In addition, the parts of the intervention that patients think are too intense to adhere to or to be unreasonable will be revised. During the intervention, we will also carefully record any suggestions given by patients and make adjustments after complete discussion.

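### Intention-to-treat is only a sensitivity analysis, no set is named for the main analysis, and the stated missing-data rules (last value carried forward, optional mean imputation) are unsound

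*Protocol article*

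**What the plan says.** All the rules stand in the Statistical analysis section of the protocol article.

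- **Main method.** "If the data are balanced, repeated ANOVA will be adopted"; otherwise GEE. No analysis set is named for either.
- **Role of ITT.** "We will use intention-to-treat (ITT) analysis to minimize bias for sensitivity analysis".
- **Dropouts within the ITT analysis.** "The results of the last measurement of the patients who drop out of the study will be taken as the effect". The sentence adds that this treats them as having finished the programme, and the GEE is then rerun.
- **Other missing data.** "missing data will be imputed with the mean values of the characteristics or with the help of multiple imputation methods", on the condition "if they are random and unrelated to the research elements". The text does not say which of the two applies when, whether the mean is taken within arm or overall, or what happens if the condition fails.

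Three other sections bear on this. Sample size allows 20% loss to follow-up and arrives at 44 per group. Study design sets assessments at baseline, T1, and 30, 90, 180 and 360 days after T1. Criteria for discontinuing or modifying allocated interventions states that "the intervention will be discontinued when the participants ask to withdraw or when their health conditions worsen".

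**The concern.** There are three separate problems.

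1. **Analysis set.** If ITT is the check, the main result may rest on a narrower set, and the text leaves that set open. Repeated ANOVA in its standard form keeps only patients with all six assessments. GEE keeps partial data but, unweighted, generally needs data missing completely at random. Either way, the primary comparison may lose the protection of randomisation.

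2. **Carry-forward as the ITT method.** Dietary behaviour is expected to change through chemotherapy and the year after it. The Discussion says that follow-up was extended to show that trend. Freezing a dropout's score removes the trend for that patient, and the error does not cancel between arms unless the arms share both trend and dropout pattern. An ITT analysis built this way cannot serve as a sound check on the main one.

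3. **Mean imputation as a permitted option.** Filled-in values at the mean add sample size but no variance. The stated condition, that data be missing at random and unrelated to the research elements, can protect the mean. It does not protect the standard error.

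**Working it through.** **The plan's dropout figure.** 36 × 1.2 = 43.2, rounded up to 44 per group, 88 in all. (Dividing by 0.8 would give 45 per group, 90 in all; the gap of 2 does not matter here.) At 20% loss, 44 × 0.8 = 35.2, so about 35 per arm are observed.

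**A. Within-arm mean imputation.** With n = 44 per arm and k observed, the filled-in data have variance s²(k−1)/(n−1), so the reported squared SE of the arm mean is s²(k−1)/[(n−1)n]. The true squared SE is σ²/k. Hence

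SE ratio = √[k(k−1) / (n(n−1))], and type I error = 2 × [1 − Φ(1.96 × ratio)].

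| Missing | k | Ratio | Type I error |
|---|---|---|---|
| 5% | 42 | √(1722/1892) = 0.95 | 6% |
| 10% | 40 | √(1560/1892) = 0.91 | 7.5% |
| 20% | 35 | √(1190/1892) = 0.79 | 12% |

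The ratio is roughly 1 minus the missing fraction and needs no assumption about the effect over time. A simulation (44 per arm, 20% dropout in each arm completely at random, no effect) agrees: reported SE 0.189 against a true 0.237, coverage about 88%, type I error about 12%.

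**B. Overall-mean imputation.** Both arms' missing values receive the same number, so the difference shrinks by the missing fraction. With a true effect of 0.5 SD and 20% missing, the loss is 0.20 × 0.5 = 0.10 SD (simulated: 0.099).

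**C. Last value carried forward.** Bias at T5 is, in each arm, the dropout fraction × (mean carried score − true T5 score), then intervention minus control. The following are assumptions, not in the documents: SD 1, within-patient correlation 0.5, last observed visit equally likely from T0 to T4, and the paths and dropout splits below. Except in the trend case, control scores are 0 at baseline and 0.2 afterwards.

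- *Effect waning 0.6, 0.45, 0.3, 0.15, 0 over T1 to T5; dropout 30% intervention, 10% control.* Intervention: carried mean (0 + 0.8 + 0.65 + 0.5 + 0.35)/5 = 0.46 against 0.2, so 0.3 × 0.26 = +0.078. Control: carried mean 0.16 against 0.2, so 0.1 × (−0.04) = −0.004. Bias +0.08 (simulated +0.07 to +0.09).
- *A simpler case.* A 0.5 SD gain at T1 fades to zero by T5, and 20% of the intervention arm leaves after T1: 0.20 × 0.5 = +0.10.
- *No effect, scores in both arms rising evenly from 0 to 1 SD; dropout 30%/10%.* Carried mean 0.4 against 1.0: 0.3 × (−0.6) − 0.1 × (−0.6) = −0.12 (simulated −0.12, type I error 8.5% to 8.9%).
- *Constant 0.5 SD effect; dropout 20% in each arm.* 0.2 × (0.56 − 0.70) − 0.2 × (0.16 − 0.20) = −0.02 (simulated about −0.02).

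The reported SE after carrying forward matched its own sampling variability (ratio 0.99 to 1.01 in the second simulation run). The fault here is bias, not a standard error that is too small.

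**D. Analysis set.** If each follow-up visit is missed independently with probability 5% or 10% (assumed), 0.95⁵ = 77% or 0.90⁵ = 59% of patients have all five follow-ups. If dropout depends on the baseline score and runs 30%/10% by arm (assumed), the simulated final-visit difference among patients with a T5 score is biased by +0.105 SD with no true effect, with 7.5% false positives.

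**E. The alternative.** A likelihood-based mixed model on all randomised patients was run in five scenarios: 20%/20% dropout with no effect, and with a constant effect; the waning effect; the time trend; and baseline-related dropout. Bias stayed within 0.012 SD, coverage was 0.948 to 0.957, and type I error was 4.3% to 5.2% where the true T5 difference was zero. The simulation took the covariance as known. All five scenarios are missing at random, so they do not test the model when dropout depends on unseen scores.

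**The case against.** Much of the case on the other side is fair.

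- **Multiple imputation is on the list.** This is correct, so the defect is an open choice between an acceptable method and a poor one. It remains a defect because the poor one is allowed and nothing decides between them.
- **The 20% loss is not what mean imputation would face.** Dropouts go to the carry-forward rule, and mean or multiple imputation covers the rest. Data collection has baseline forms checked on the spot and electronic forms that require every item, so the rest may be small, though missed visits remain possible. The 5% row may be nearer the mark, and 12% is an upper illustration. The phrase "missing data will be imputed with the mean values of the characteristics" may even refer to demographic and clinical variables rather than DMBQ scores. The text does not settle this.
- **GEE is the fallback.** A reader might infer that the main result certainly rests on completers. The article does not say so: it names no set, and the word balanced follows directly on baseline comparisons and distribution checks. If it means balanced repeated measures, missed visits lead to GEE, which uses partial data. The exclusion of randomised patients is a possibility left open, not a stated rule.
- **Outcome-related dropout is not established.** The discontinuation criterion ends the intervention, not the assessments, and worsening health is not the DMBQ. A link is plausible, but the documents do not show it.
- **Carry-forward bias has no fixed direction.** A reader might infer that it always favours the intervention, or that it also makes the standard error too small. Section C of the working supports neither.

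**Conclusion.** The point stands in this form. ITT is given only a sensitivity role and the main set is unnamed. The ITT analysis relies on carrying last values forward, which can bias the 12-month comparison either way. Single mean imputation is permitted with no rule for preferring multiple imputation.

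The firmest figure is the standard-error shortfall under within-arm mean imputation, which depends only on the missing fraction and on the mean being taken within arm. The carry-forward biases (about +0.10 to −0.12 SD) and the complete-case figures rest on assumed paths, dropout splits and per-visit loss, and show plausible size rather than a prediction. These are rules that the article states, not detail left to a fuller document, and they govern the primary endpoint.

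**What to change.** 1. Define the primary analysis as all randomised patients in their assigned arm, using every observed DMBQ score in a likelihood-based mixed model for repeated measures. Multiple imputation is an acceptable alternative; choose one in advance.
2. Delete the mean-imputation option.
3. Stop using last value carried forward as the ITT method. Keep it, if at all, as a labelled secondary sensitivity analysis.
4. Add a sensitivity analysis for data missing not at random, over a range of shifts stated in advance.
5. Report completers as supportive only.

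The cost is analysis wording, since the follow-up contacts are already planned. Intervals become somewhat wider: at 20% dropout per arm the mixed-model SE is 0.230 SD, against 0.212 with carry-forward and 0.189 as reported after within-arm mean imputation.

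### The dropout sensitivity analysis is fixed to GEE even where the main analysis is repeated ANOVA, so a changed P value cannot be credited to dropout alone

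*Protocol article*

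**What the plan says.** All the relevant text is in the Statistical analysis section of the protocol article.

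- Main model, first branch: "If the data are balanced, repeated ANOVA will be adopted".
- Main model, second branch: "Otherwise, we will use a generalized estimating equation (GEE) to analyze the intervention’s time, group, and interaction effects".
- Role of intention-to-treat: "We will use intention-to-treat (ITT) analysis to minimize bias for sensitivity analysis".
- Dropouts in that analysis: "The results of the last measurement of the patients who drop out of the study will be taken as the effect", that is, last observation carried forward (LOCF).
- Model for that analysis: "and the analysis will be reconducted with the GEE". No condition is attached, and nothing provides for repeating the ANOVA where ANOVA was the main model.
- A further rule says that "missing data will be imputed with the mean values of the characteristics or with the help of multiple imputation methods", if the gaps are random. It is not assigned to the main or to the sensitivity analysis.
- Decision rule: "the α level will be 0.05, and the tests will be two-sided".

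'Balanced' is not defined. The sentences just before it concern baseline comparability of the arms and a normality check. The Sample size section allows for 20% loss to follow-up and arrives at 44 patients per group.

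**The concern.** A sensitivity analysis for dropout is informative when it changes the missing-data assumption and nothing else. On the ANOVA branch, this plan also changes the test, from an ANOVA F test to a GEE Wald test. The two tests can give different verdicts on the same records. A non-significant main result could become significant in the intention-to-treat analysis, or the reverse, with no contribution from the missing values. Because the plan judges results against 0.05, a reader would naturally take such a change as evidence about dropout. The robustness statement for the primary outcome, the Dietary Management Behavior Questionnaire score, is what is at stake.

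**Working it through.** **1. Which branches are affected**

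| Meaning of 'balanced' | Main model when patients drop out | Sensitivity model | Like for like? |
|---|---|---|---|
| Baseline balance or distribution, satisfied | Repeated ANOVA | GEE | No |
| Baseline balance or distribution, not satisfied | GEE | GEE | Yes |
| Every patient measured at every visit | GEE (ANOVA only if nobody drops out) | GEE | Yes |

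Only the first row is a problem. Randomised arms will usually look balanced at baseline, so under that reading it is the expected row. The planned loss is 0.20 × 88 = 17.6, or about 18 patients.

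**2. What the change of model moves**

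On a complete rectangular data set, both models with group, time and interaction terms estimate the same cell means. In 300 simulated trials, the largest difference between ANOVA and GEE mean differences was below 1e-15. The average 12-month effect was 0.500 SD in completers and 0.475 SD after LOCF, under either model. A shift in the estimate therefore comes from the data handling, while standard errors and P values also depend on the model.

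**3. How often the test alone changes the verdict**

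The documents state no figure on this, so it was simulated with no missing data, applying both tests to identical records.

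- From the documents: 44 per arm; six visits; two-sided 0.05; visit times 0, 2, 3, 5, 8 and 14 months (baseline, the end of the 8 weeks taken as 2 months, then 1, 3, 6 and 12 months later).
- Assumed: a constant post-baseline shift of 0 to 0.5 SD, and a within-patient correlation of either 0.6 throughout or 0.3 + 0.7 × 0.6^(gap/3 months). The second gives 0.89 for a 1-month gap and 0.37 for a 14-month gap.
- ANOVA: F = (SS_interaction/5) / (SS_error/430), since (88 − 2) × 5 = 430, with both degrees of freedom multiplied by the Greenhouse-Geisser epsilon.
- GEE: W = b′V⁻¹b, with b the five interaction terms and V their robust covariance, referred to chi-square on 5 df.

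Share of 6,000 trials per setting in which the two tests disagree at 0.05:

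| Shift (SD) | 0 | 0.2 | 0.3 | 0.4 | 0.5 |
|---|---|---|---|---|---|
| Common correlation | 4.0% | 6.2% | 8.7% | 9.2% | 7.2% |
| Decaying correlation | 6.3% | 16.1% | 25.1% | 30.8% | 25.4% |

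A repeat with new random numbers gave 4.1 to 9.8% and 6.8 to 30.7%. Without the Greenhouse-Geisser correction, the ranges are 4 to 8% and 7 to 23%. In 75 to 98% of disagreements, GEE was significant and ANOVA was not. With no true effect, GEE rejected in about 8% of trials and ANOVA in 4 to 5%.

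**4. With dropout: the plan against a fixed model**

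Here the main analysis is assumed to be ANOVA on completers. The figures are the share of trials whose verdict differs between the main and the sensitivity analysis.

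| Setting | LOCF with GEE (as written) | LOCF with ANOVA (model held) |
|---|---|---|
| 20% random dropout, common correlation | 6 to 18% | 4 to 16% |
| 20% random dropout, decaying correlation | 8 to 38% | 2 to 18% |
| 20% dropout concentrated in low baseline scores, correlation 0.5, shift 0.5 SD (300 trials) | 18.3% | 14.7% |

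In the last setting, changing only the model altered 11.0% of verdicts on completer data and 7.7% on LOCF data. The net difference in that row is 18.3 − 14.7 = 3.6 percentage points. With 300 trials, the standard error of the 18.3% alone is √(0.183 × 0.817/300) = 2.2 points.

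**The case against.** The strongest reply is that in repeated-measures work 'balanced' often means that every patient is measured at every visit. ANOVA would then run only when there is nothing to carry forward. With 20% loss expected, GEE would be the main model, and the sensitivity analysis would simply repeat it. The text permits this reading, and under it the point falls away. It is the less natural one here, because the word follows directly on the baseline comparison and the normality check.

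Three further objections stand in part.

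- A reader might infer that the sensitivity analysis cannot show whether dropout matters, or that it is uninterpretable. The documents do not support that. Effect estimates remain comparable, and only tests, P values and intervals are mixed with the change of model.
- A reader might also infer that the two analyses necessarily include different patients. The article does not state which patients enter the main analysis, and the imputation rule is assigned to neither analysis. Completers-only is an assumption in step 4.
- The size is uncertain. Many changed verdicts remain when the model is held fixed, as they should if dropout has an effect. With a common correlation the excess due to the model is small. The figures near 30% need the decaying correlation and a particular shift. The tilt toward GEE reflects its higher rejection rate in general, not anything specific to dropout.

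None of this makes the comparison like for like on the ANOVA branch.

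**Conclusion.** The point holds conditionally. If 'balanced' refers to baseline balance or distribution, and patients drop out, the plan changes the test and the missing-data handling together. A change in P value or significance between the main and the sensitivity analysis cannot then be credited to dropout alone. Agreement on significance is also weaker reassurance than it looks, since the second test rejects more readily in these simulations. The change of test alone alters the verdict in roughly 4 to 9% of trials under a common correlation of 0.6, and in up to about 30% under the decaying correlation, mostly toward significance under GEE. These sizes rest on assumed correlations and shifts that the documents do not give, so they show direction and order of magnitude only. There is no problem if 'balanced' means complete data or if GEE is the main model. The correction should be made because it costs almost nothing and protects the robustness statement for the primary outcome.

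**What to change.** Replace the clause that ties the sensitivity analysis to GEE with wording such as: 'The sensitivity analysis for dropouts will use the same model, terms and test as the main analysis; only the handling of missing data will differ.' Naming one model for both analyses would serve equally well. Define 'balanced' in the same place, so that the reader knows which branch applies when patients drop out. If GEE is kept for the sensitivity analysis, run it on the main-analysis data as well. Main ANOVA against main GEE then shows the effect of the model, and main GEE against LOCF GEE shows the effect of the missing data. The cost is one sentence, a short definition and one extra model run, with no new data or patients.
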